# Physical inactivity and sedentary behaviours: screening and intervention in primary care, *a prospective*,* multicentre*,* cluster-randomised*,* controlled*,* stepped-wedge study*

**DOI:** 10.1186/s12889-025-25410-4

**Published:** 2025-11-14

**Keywords:** Primary care, General practitioner, Physiotherapist, Physical activity, Physical inactivity, Sedentary lifestyle, Serious game, RCT

## Abstract

**Background:**

Physical inactivity and sedentary behaviours (PiA/SED) are among the major modifiable risk factors for chronic diseases. Behaviour change models for PA can shape personalised interventions leading to sustainable lifestyle changes. We hypothesise that screening for PiA/SED by a general practitioner, followed by a personalised intervention by a physiotherapist, could reduce PiA/SED in inactive adults.

**Methods:**

We designed a prospective, multicentre, cluster-randomised, controlled, step-wedge study. Adult patients without chronic illnesses will be recruited in 8 multi-professional health centres. They will receive educational content on PiA/SED. During the intervention periods, patients will see a physiotherapist for a functional assessment, and an intervention aimed at improving PiA/SED using a serious game. Two follow-up appointments at months 2 and 4 (M2-4) are planned to maintain patient motivation. At M6, a 7-day actimetry will be performed, and at M6-12, questionnaires and semi-structured interviews will close the study. Two primary endpoints will be analysed using a pre-specified hierarchical sequential analysis: the proportion of patients changing PiA/SED at M6. Secondary objectives include: 1-describing changes in PiA/SED at M6 and M12, 2-exploring the link between patient characteristics and changes in PiA/SED, 3-describing participants’ quality of motivation, satisfaction of basic psychological needs, feelings of self-efficacy, perceived levels of vitality and energy, and self-esteem, 4-describing the strategies, barriers and facilitators of behavioural changes, 5-studying the correlation between questionnaires measuring physical activity and actimetry, 6-identifying the perceived barriers and facilitators to implement this care pathway. Assuming that 10% of patients in the control period will improve their PA and that the intervention will increase it by 20%, 160 patients provides 82% power to observe a significant difference.

**Discussion:**

This design will harmonise the skills of all professionals in the field of motivational support for PiA/SED and providing information about the risks associated with PiA/SED. Patients in the intervention group will also receive individual support for behaviour changes related to PiA/SED. Considering public health, this study will contribute to increase primary prevention by healthcare professionals. Finally, this study will assess the effectiveness, adherence, satisfaction of the stakeholders involved in this pathway allowing to consider its implementation in routine primary care.

**SPIRIT 2025 checklist of items:**

see supplement files.

**Trial registration:**

ClinicalTrials n° NCT06678906, https://clinconnect.io/trials/NCT06678906#about-company-tab, first registration October 14, 2024, Trial updated February 05, 2025.

**Supplementary Information:**

The online version contains supplementary material available at 10.1186/s12889-025-25410-4.

## Background

Physical inactivity (PiA) and sedentary behaviour (SED) are major risk factors for several chronic diseases and premature mortality [1–3]. Globally, 7.2% of deaths from all causes and 7.6% of cardiovascular diseases are attributable to PiA based on data collected from 168 countries in 2018 [1,4]. While often associated together, PiA and SED are distinct behaviours, each with their own health effects [5]. This distinction highlights four possible profiles: active yet sedentary, active and non-sedentary, inactive and sedentary, and inactive yet non-sedentary. In France in 2015, a national survey reported low physical activity (PA) and high SED in 37% and 80% of people aged 18 to 79 respectively [6, 7].

As these are modifiable risk factors [8], healthcare professionals, more particularly primary care general practitioners (GP) and physiotherapists (PT) are well positioned to promote physical activity, as shown in a 2022 meta-analysis [9]. However, of 46 randomized controlled trials included, only 14 measured physical activity through devices among which no significant increases in moderate to vigorous physical activity were observed [9]. Additionally, interventions should incorporate well-described and coherent behavioural change models such as the Health Action Process Approach [10], the Multi-Process Action Control in Physical Activity Model [11] and the theory of effort minimisation [12].

We propose that an innovative healthcare pathway, involving opportunistic screening by GPs and short, individualized and pragmatic interventions by PTs based on behavioural change models, can effectively facilitate behaviour changes towards increased PA and reduced SED at six months in inactive adults not already suffering from chronic illnesses.

## Method

### Primary aim and outcomes

The primary objective is to evaluate the 6-month effectiveness of an innovative care pathway that includes opportunistic screening for PiA and SED by a GP, followed by a personalized intervention by a PT on PiA/SED for adult patients not already suffering from chronic illnesses reimbursed by the French Social Security system.

Two main criteria will be analysed, according to a predefined hierarchical sequential analysis as follows: (1) the proportion of patients changing PA category (inactive, moderately active, very active), measured by actimetry, between inclusion (M0) and the sixth month (M6), to a higher-ranking category; (2) the proportion of patients changing SED category (sedentary, non-sedentary), measured by actimetry, between M0 and M6, to a lower-ranking category.

PA and SED will be measured at inclusion, M0 and at M6 post-intervention from a 7-day actimetry performed with the wGT3X-BT device, Actigraph, Pensacola, USA. PA profiles are defined as: inactive < 600 MET.min/week; moderately active < 1200 MET.min/week; very active ≥ 1200 MET.min/week^8^. Sedentary behaviour is defined as time spent lying or sitting without sleeping with energy expenditure close to resting (≤ 1.5 METS) [8]. The threshold of 9 h/day of sedentary behaviour is considered due to its association with an increased all-cause mortality risk [13].

### Secondary aims and outcomes

Secondary objectives include: (1) describing the evolution in PA and SED of patients at M6 and M12 for behaviour maintenance; (2) exploring the relationship between patient characteristics, such as age, sex, socioeconomic status, environment, living area, and occupation, and the change at M6 and maintenance at M12 of PiA and SED; (3) describing the quality of motivation, satisfaction of basic psychological needs, sense of personal effectiveness, perceived vitality and energy level, and self-esteem; (4) describing at M6 and M12 the strategies, barriers, and levers to behavioural change through semi-structured interviews, coupled with a qualitative survey *via* semi-structured interviews on a volunteer subsample of 25% of participants, who may or may not have benefited from the intervention at M6 and M12; (5) studying the relationship between the ONAPS-PAQ questionnaire [14] results and the 7-day actimetry among the inactive and/or sedentary population category; (6) identifying perceived barriers and facilitators to implementation in primary care at 12 months among different stakeholders, including GPs, PTs, and patients.

Outcomes for PA and SED will be measured at M6 by a 7-day actimetry and at M12 by the ONAPS-PAQ questionnaire [14]. Secondary aim number 3 will be measured through five questionnaires: *Echelle de Motivation envers l’Activité Physique en contexte de Santé* (EMAPS) [15], scale measuring basic psychological needs [16], scale measuring perceived competence to engage in a personalized physical activity program [17], scale measuring perceived vitality and energy level [18], and the self-esteem scale [19] at M0, M6, and M12.

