### Population

The study involves adults not suffering from chronic illnesses reimbursed by the French Social Security system, receiving outpatient primary care from one of the 8 participating multi-professional health centres (MPHC). These individuals are classified as inactive, regardless of being sedentary or non-sedentary, based on the ONAPS-PAQ questionnaire and ultimately by actimetry. Participants signed an informed consent to be part of the study and were confirmed inactive after the analysis of 7-day accelerometry data.

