### Setting and design

We designed a prospective, multicentre, randomised, cluster-controlled step-wedge [20] study in 8 MPHC dedicated to primary care within Auvergne Rhône-Alpes area in France.

Pre-Inclusion: during a routine appointment with a GP at a participating MPHC, the patient is invited to complete the ONAPS-PAQ questionnaire using a REDCap survey via a QR code on a study information poster in the waiting room or by the doctor’s secretary. During the consultation, after verifying the inclusion criteria thanks to the questionnaire results, the GP presents the study to patients classified as “inactive” according to the ONAPS-PAQ. At this stage, the patient is further tested for eligibility by completing a 7-day actimetry for definitive inclusion. Consent to participate of each participant is collected accordingly to the National Biomedical Ethics Committee North-West 3 clearance, under the number N° ID/RCB : 2024-A00983-44.

Inclusion: at home, the patient completes the questionnaires, scales online, and provides demographic information (self-entry using the REDCap software). The patient receives the accelerometer at home along with all necessary instructions. They are required to wear it for 8 consecutive days (accelerometry is measured over 7 days) and simultaneously maintain a log detailing the start and end times of wear, any periods of non-wear, and any naps taken during the day.

While all enrolled patients will receive standard information on PA and SED (intervention step 1), only patients in the intervention group will receive a functional assessment and personalized behaviours change intervention. The intervention consists of a serious game (step 2) during an individual appointment with a PT at the MPHC and remote coaching at M2 and M4 (step 3), as shown in Fig. 1. During follow-up visits at M6 and M12, patients will be required to complete questionnaires and scales, and some will also participate in semi-structured interviews. The objectives and questions for the semi-structured interviews will be the same at M6 and M12, with the same participant being interviewed at both M6 and M12 by the same investigator. The visit conducted at M12 will be the end-of-study visit.

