#### Statistical analysis

A stepped-wedge design (Fig. 1) with 5 time periods and 4 steps, involving 8 centres transitioning from the control period to the experimental period (2 centres per step), with an average of 20 patients per centre (approximately 4 patients per centre per time period), results in a total sample size of 160 patients.

This design provides 82% power to detect a significant difference between the groups at the first level of the hierarchy (PASS v22, NCSS, LLC, Kaysville, Utah, USA). This calculation is based on the method described by Hemming et al. [22], which uses a linear mixed-effects model with time as a fixed factor at T levels and inter-cluster variation modelled as a random effect. The test statistic employed is a two-sided z-test. Our assumptions leading to this conclusion are that the intervention increases the proportion of patients changing their physical activity profile, corresponding to the first level of the hierarchy, by 20% (in absolute value), assuming that 10% of patients in the control period will experience an improvement. The intraclass correlation coefficient (ICC) is 0.01, and the significance level of the test is 0.05.

For each of the two groups, qualitative variables will be described by their count and percentage, while quantitative variables will be characterized by their mean and standard deviation, or median and interquartile range if they do not follow a normal distribution. The normality of quantitative variables will be assessed by graphical inspection and the Shapiro-Wilk test. The primary analysis does not plan to impute missing data. However, we propose the following strategy currently recommended [23] to minimize the impact of missing data as much as possible: reduce attrition to a minimum by limiting constraints (number of site visits, etc.), continue patient follow-up and outcome collection even in cases of protocol deviations, and consider sensitivity analyses on the per-protocol population, as well as on the ITT population after replacing missing data by multiple imputation methods, provided the assumption of missing at random (MAR) is credible.

A detailed statistical analysis plan will be drafted before the database lock. It will take into account any protocol amendments or unexpected events that occurred during the study and impacted the analyses presented above. The planned analyses may be supplemented in alignment with the study objectives.

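### Maintenance of activity and sedentary behaviour from M6 to M12 is described with actimetry at M6 and a questionnaire at M12, so behaviour change cannot be separated from instrument disagreement

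*Protocol article*

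**What the plan says.** All references are to the protocol article.

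- **Aims.** Under 'Secondary aims and outcomes', aim 1 is "describing the evolution in PA and SED of patients at M6 and M12 for behaviour maintenance". Aim 2 explores how patient characteristics relate to "the change at M6 and maintenance at M12 of PiA and SED".
- **Instruments.** The same section fixes the measure for each visit: "Outcomes for PA and SED will be measured at M6 by a 7-day actimetry and at M12 by the ONAPS-PAQ questionnaire". No actimetry is stated at M12.
- **Primary endpoints.** Under 'Primary aim and outcomes', "PA and SED will be measured at inclusion, M0 and at M6 post-intervention from a 7-day actimetry". That comparison stays within one instrument.
- **Entry.** Under 'Population', patients are classed as inactive "based on the ONAPS-PAQ questionnaire and ultimately by actimetry". 'Setting and design' shows that the ONAPS-PAQ is completed before inclusion.
- **Link between the instruments.** Aim 5 is "studying the relationship between the ONAPS-PAQ questionnaire [14] results and the 7-day actimetry among the inactive and/or sedentary population category".
- **Other follow-up forms.** 'Setting and design' says: "During follow-up visits at M6 and M12, patients will be required to complete questionnaires and scales". The five scales for aim 3 are named with their time points, and the ONAPS-PAQ is not among them. The readable text does not name the ONAPS-PAQ at M6.

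**The concern.** Maintenance is a statement about the same quantity at two times. Here the only PA and SED measures named for those times are a 7-day device recording at M6 and a self-report questionnaire at M12. A patient who behaves identically at both visits can still change category because the two instruments classify that behaviour differently.

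The protocol does not treat the instruments as equivalent. It requires actimetry to confirm a questionnaire result at entry, and it makes their relationship a study aim. If no matching measure is collected, no later analysis can restore a like-for-like M6-to-M12 comparison. At stake is whether aims 1 and 2 can say anything about relapse or late gain after M6.

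**Working it through.** The plan gives no figure on this point, so there is nothing to reproduce. The check first sets the text side by side and then illustrates the size.

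**Could another stated element separate the two sources of change?**

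1. *ONAPS-PAQ at screening with ONAPS-PAQ at M12.* This is like for like, but it spans entry to M12 and does not isolate M6 to M12. It also starts from patients selected as inactive on that questionnaire, so regression to the mean would tend to inflate the apparent gain.
2. *Aim 5 as a calibration.* It is limited to the inactive and/or sedentary category, has no stated time point and is not described as a calibration. Maintenance concerns patients who have moved to a more favourable category, and those who are neither inactive nor sedentary fall outside aim 5.
3. *ONAPS-PAQ at M6.* This would allow a one-instrument comparison, but the readable text does not state it.

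**Illustration of size, for the PA category**

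Inputs:

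- p, the share improved by actimetry at M6. 'Statistical analysis' gives 10% for control, "assuming that 10% of patients in the control period will experience an improvement", and an absolute increase of 20 points, hence 30% with the intervention. These are planning values, used only for illustration.
- Se and Sp, the sensitivity and specificity of the ONAPS-PAQ for 'improved', with actimetry as reference. The documents give neither. The range 0.7 to 0.9 for each is an assumption.
- Behaviour is taken as unchanged between M6 and M12.

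Formulas:

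- Apparent share improved at M12 = p × Se + (1 − p) × (1 − Sp)
- Apparent shift = that share − p

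| p | Se | Sp | Apparent share at M12 | Apparent shift |
|---|---|---|---|---|
| 0.30 | 0.7 | 0.9 | 0.21 + 0.07 = 0.28 | −2 points |
| 0.30 | 0.8 | 0.8 | 0.24 + 0.14 = 0.38 | +8 points |
| 0.30 | 0.9 | 0.7 | 0.27 + 0.21 = 0.48 | +18 points |
| 0.10 | 0.7 | 0.9 | 0.07 + 0.09 = 0.16 | +6 points |
| 0.10 | 0.8 | 0.8 | 0.08 + 0.18 = 0.26 | +16 points |
| 0.10 | 0.9 | 0.7 | 0.09 + 0.27 = 0.36 | +26 points |

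At the individual level, 1 − Se = 10% to 30% of those improved at M6 would appear to have relapsed. Likewise 1 − Sp = 10% to 30% of those not improved would appear to be late improvers.

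If Se and Sp are the same in both groups, a fully maintained 20-point difference would be seen as 20 × (Se + Sp − 1). That is 20 × 0.4 = 8 points to 20 × 0.8 = 16 points, so the difference is diluted and not created.

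Setting Se = Sp = 1 gives a shift of 0 for both values of p. This says only that the component due to switching instrument disappears. Repeated use of either instrument still carries week-to-week variation and measurement error.

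**The case against.** The strongest reply has four parts.

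1. **The data-collection table is not shown, and the article is condensed.** The ONAPS-PAQ may already be among the M6 questionnaires. This stands as a limit: in that case no data need be added. The wording would still need correcting, because the text names actimetry as the M6 outcome.
2. **A direct comparison of M12 questionnaire categories with M6 actimetry categories is not stated.** This is also true. Each follow-up could be read against its own baseline, actimetry from M0 to M6 and ONAPS-PAQ from entry to M12. That reading is possible, but it does not yield maintenance between M6 and M12 and brings in the regression to the mean noted above.
3. **The aims are modest.** Aim 1 describes and aim 2 explores. A reader might infer that a between-group test of maintenance would be biased. The readable text states no such test, so that claim is not supported. Unequal reporting by coached patients is a plausible limitation of the M12 self-report and no more than that.
4. **The size is assumed.** A reader might take an individual disagreement rate between the instruments and set it beside the 20-point planned effect. The two are not comparable: disagreement runs in both directions and partly cancels, whereas the 20 points is a net between-group difference in M0-to-M6 improvement. The net shift in the table can be close to zero.

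A reader might also infer that actimetry overrules the questionnaire at entry. The text describes a sequence in which both must show inactivity. Actimetry can exclude a patient whom the questionnaire classed as inactive, but it cannot admit one whom the questionnaire classed as active.

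**Conclusion.** The point holds for secondary aims 1 and 2. On the readable text, PA and SED come from different instruments at M6 and M12, and nothing stated allows instrument disagreement to be removed from an M6-to-M12 change.

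Under assumed sensitivity and specificity of 0.7 to 0.9 and unchanged behaviour, the apparent net shift is about −2 to +18 points at p = 30% and +6 to +26 points at p = 10%. These figures depend wholly on the assumed agreement and on the protocol's planning proportions for PA. They do not carry over to SED, for which no planning proportion is given.

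The primary endpoints are untouched. This is a cheap improvement to secondary outcomes, and it lapses to a wording change if the ONAPS-PAQ is already collected at M6.

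**What to change.** - Give the ONAPS-PAQ at M6 as well as at screening and M12, unless the data-collection table already has it there.
- Define M6-to-M12 evolution and maintenance, for aims 1 and 2, within the ONAPS-PAQ only.
- Keep actimetry for the M0-to-M6 comparison.
- State that PA and SED categories are not compared across instruments.
- State two limitations: maintenance remains self-reported, so any reporting bias in coached patients is not removed; and gains counted from the screening ONAPS-PAQ are exposed to regression to the mean.

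The cost is at most one short online form at a visit where patients already complete questionnaires, plus revised outcome wording. Repeating the 7-day actimetry at M12 would also keep one instrument and would avoid self-report, but it adds a further device-wearing period for every patient.

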### Population

The study involves adults not suffering from chronic illnesses reimbursed by the French Social Security system, receiving outpatient primary care from one of the 8 participating multi-professional health centres (MPHC). These individuals are classified as inactive, regardless of being sedentary or non-sedentary, based on the ONAPS-PAQ questionnaire and ultimately by actimetry. Participants signed an informed consent to be part of the study and were confirmed inactive after the analysis of 7-day accelerometry data.

### Setting and design

We designed a prospective, multicentre, randomised, cluster-controlled step-wedge [20] study in 8 MPHC dedicated to primary care within Auvergne Rhône-Alpes area in France.

Pre-Inclusion: during a routine appointment with a GP at a participating MPHC, the patient is invited to complete the ONAPS-PAQ questionnaire using a REDCap survey via a QR code on a study information poster in the waiting room or by the doctor’s secretary. During the consultation, after verifying the inclusion criteria thanks to the questionnaire results, the GP presents the study to patients classified as “inactive” according to the ONAPS-PAQ. At this stage, the patient is further tested for eligibility by completing a 7-day actimetry for definitive inclusion. Consent to participate of each participant is collected accordingly to the National Biomedical Ethics Committee North-West 3 clearance, under the number N° ID/RCB : 2024-A00983-44.

Inclusion: at home, the patient completes the questionnaires, scales online, and provides demographic information (self-entry using the REDCap software). The patient receives the accelerometer at home along with all necessary instructions. They are required to wear it for 8 consecutive days (accelerometry is measured over 7 days) and simultaneously maintain a log detailing the start and end times of wear, any periods of non-wear, and any naps taken during the day.

While all enrolled patients will receive standard information on PA and SED (intervention step 1), only patients in the intervention group will receive a functional assessment and personalized behaviours change intervention. The intervention consists of a serious game (step 2) during an individual appointment with a PT at the MPHC and remote coaching at M2 and M4 (step 3), as shown in Fig. 1. During follow-up visits at M6 and M12, patients will be required to complete questionnaires and scales, and some will also participate in semi-structured interviews. The objectives and questions for the semi-structured interviews will be the same at M6 and M12, with the same participant being interviewed at both M6 and M12 by the same investigator. The visit conducted at M12 will be the end-of-study visit.

